### Equipment

This study will employ a planar or 2-dimensional (2D) table-top rehabilitation robotic device (H-Man, Articares Pte Ltd) [30] that has a robotic handle resembling an ergonomic computer mouse. The robotic device will be placed on a height-adjustable table and linked via a network cable to a computer with a 24-inch LCD display (Dell OptiPlex 7470 AIO, Intel Core i7-9700 with 3 GHz CPU, 16 GB RAM, and 64-bit Windows 10). The 2D coordinate of the handle will be captured and recorded by the computer through a custom-made software coded in MATLAB R2019b (MathWorks Inc., Natick, MA, USA). The software also provides an interactive gaming interface which corresponds to the 2D workspace of the robotic device, shown on the LCD display. An ergonomic upper limb support (MoMo, Reharo Corp.) will be used to provide support to the elbow to prevent fatigue. A custom-made rectangular box is placed on top of the robotic setup to block the vision of the arm (Fig. 3a). Participants will be seated on a clinical chair in front of the robot with their body securely strapped onto the chair. The affected elbow will be flexed to ∼90°, the forearm pronated to ~45°, and the hand gently placed on the robotic handle secured with a Velcro strap. The initial position of this handle, which is in the middle of the horizontal axis of the workspace, determines the start location during the session. The body alignment will be set in such a way that the handle is roughly in front of the affected shoulder midline.

**Fig. 3 Fig3:**
[figure not shown]
Experimental setup used in the study. **a** A compact table-top rehabilitation robotic device with the rectangular box covering the view of the affected arm. An example of feedback shown on the LCD display following a successful trial (**b**) and unsuccessful trial (**c**), respectively. Note: the person depicted is not a patient, but a study team member

### Intervention design

Participants in each group will receive 15 individual, face-to-face sessions of robotic-based training by a certified therapist for a maximum of one hour per session. The same therapist will be in charge of administering the whole intervention sessions to every participant and assuring adherence to the protocol. Each training session will begin with a warm-up exercise, after which participants will continue with the active somatosensory training task or motor-based control task depending on the group they are assigned to. In the first training session, there will be some familiarisation trials with instructions for ten repetitions before the actual training commences.

#### Warm-up exercise

This session entails two warm-up exercises with the use of robotic device to prepare the sensorimotor system for the subsequent training task. On the LCD display, a black screen will be shown together with a circular indicator to denote a start position of the movement (1.2 cm diameter, 2 mm thickness). A smaller white circle (0.8 cm diameter) will represent the position of the handle in the workspace, which will always be shown on the LCD display. To familiarise with the robotic setup, participants will begin the session by moving the robotic handle towards a visual object shown on the monitor screen, according to the range of motion of their UL for about 5 min. Following this, the robotic handle will move back to the start position again, after which participants will perform the second warm-up exercise that mimics the joint approximation technique. In this exercise, the robot will produce a spring-like resistive force (stiffness = 900 N/m) which is position-dependent while the participants are moving in the direction of the target, meaning the resistance will increase as the handle is getting nearer to the target location. They will be told to pay attention to the resistive force preventing them to move towards the corresponding target location. The distance between the two adjacent points is 10 cm. Audio feedback will be provided if the movement has reached the target, after which the position will be locked for 2 s before starting the next repetition. The duration of this task is 16 repetitions.

#### Active somatosensory training task

The treatment group will participate in the active somatosensory training as follows. Participants will be instructed to propel the robotic handle with their affected UL from the start position to one of the target positions. On the LCD display, a gaming interface will be shown together with the white handle position and the start position indicator. However, they will be informed that this white circle will disappear once the handle is moved 2 cm away from the centre of the start position. There will be four different target positions located 15 cm equidistant from the start position, at an angle of 30°, 60°, 120°, and 150° with respect to the horizontal axis. Each of these positions will be presented an equal number of times in one of the two fixed, repeated sequences that either starts from 30° to 150° or from 150° to 30°. The sequences will be alternatively varied across blocks. A circular visual target in the form of a cartoon character will appear at one of the positions as shown on the LCD display, with a 440 Hz tone as a movement initiation cue. Participants will begin reaching towards the target only after this cue and will be asked to produce the movement as straight as possible. Participants will be told about the augmented feedback that will help them learn the desired path to reach the target (see below, ‘Augmented feedback’). The view of the active forearm will be occluded using a rectangular box, and there is no visual indicator of the handle whatsoever on the LCD display. Thus, they will perform the task by relying more on somatosensory cues of their upper limb in space.

Once the movement is completed the robot will hold the position for 2 s, during which augmented feedback will be given in two kinds. Following the feedback, the robot will bring the hand back to the start position in 10 cm/s while the UL remains relaxed. This returned trajectory will follow a smooth and straight path according to the minimum jerk model in [31] (stiffness = 3500 N/m, damping = 20 N.s/m). The next repetition will continue after a brief interval of 1.5 s. Each session comprises ten blocks of 24 repetitions. Note that participants will be given a short break in between consecutive blocks, or if the therapist notices decreased movement quality in them.

#### Augmented feedback

Prior studies which enhance somatosensory information and provide positive feedback have uncovered less movement error and improved somatosensory acuity in participants by reinforcing successful performance and providing motivational boost [15, 16]. In a similar fashion, the current training will be facilitated by the presence of two kinds of augmented feedback (Table 1). The first feedback will be available concurrently while the participants perform the movement. This online feedback will be perceived as a ‘virtual wall’ produced by the robot handle (stiffness = 1000 N/m) along the path connecting the start position and the target. Such kind of haptic feedback can serve as somatosensory cues to the active arm while participants are moving towards the corresponding target. If the movement deviates too much from the trajectory, they will feel a cushion-like force preventing the handle to move further away from the ideal path.

**Table 1 Tab1:** Augmented feedback used during training

Type of feedback	Content (source)	Schedule	Purpose	Treatment	Control
Somatosensory cues	Virtual wall during movement (force produced by the robot handle)	Concurrent	Haptic guidance, through feeling to enhance participation	√	
Visual cues	Handle position as a cursor (on LCD display) and vision of the affected arm	Concurrent	Provide hand position in real-time		√
Performance	Trajectory of the previous movement (on LCD display)	Terminal (successful and unsuccessful)	Improve subsequent performance, and for • corrective action	√	√
Outcome	Pleasant tone, scores, words of encouragement (LCD display and speaker)	Terminal (successful)	• Motivation, positive reinforcement	√	√

The second feedback will be available at the end of each movement that informs the participants how good the latest movement has been performed. This terminal feedback will be displayed as a trajectory of the movement made, together with a reference line connecting the start position and the target centre. Another kind of terminal feedback will be given only following every successful movement outcome as positive feedback. Here, a green-coloured text with a running score will be shown on the LCD display together with a pleasant audio tone. At random intervals, positive words in the form of audio feedback (e.g. ‘Good job!’, ‘Well done!’, or ‘Excellent!’) will also be played as additional reward or reinforcement. No positive feedback will be given if the movement is unsuccessful, although the handle trajectory will still be shown as information to improve subsequent performance.

The size of the visual targets for reaching will determine the provision of positive feedback after each successful outcome. A movement outcome is considered successful based on two criteria, i.e. if the endpoint error *and* lateral perpendicular deviation are within the span of the target. The diameter of each target is set to 3.0 cm and will remain fixed across sessions.

#### Motor-based control task

A control group will be introduced as a comparison to examine whether any observed improvements in the performance are strictly due to the proposed training task. Participants in this group will also take part in the robotic-based training with some important differences. The same centre-out reaching movements will be used, but without any emphasis on proprioception or kinaesthesia. Here, the view of the forearm will not be blocked, and the handle position will always be shown on the LCD display (Table 1). Other feedback such as running score and positive feedback will still be provided to inform the participants of their trial outcomes, but no somatosensory cues (haptic guidance) will be given while they are actively moving. They will complete this motor-based training for the same number of sessions and repetitions as the treatment group, with the same assessments conducted before and after the whole training.

### Primary outcome measures

Two robotic-based tests will generate behavioural performance indices as the primary outcome measures of participants’ affected UL before (baseline) and after training (post-day 1 and post-day 30).

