#### Kinaesthetic test

Following the motor test, participants will perform the kinaesthetic test that is essentially a joint position matching task [32], which requires them to reproduce a reference movement presented to the affected arm. The test evaluates the ability to dynamically feel the sensation of movement, as well as, to perceive the endpoint position of the reference trajectory in the absence of the vision of their affected forearm.

In the beginning of every trial, participants will be instructed to remain relaxed while the robot displaces their hand forward and backward towards a certain target position with a smooth and straight trajectory production, with a speed of 10 cm/s. Once the robot completes this reference movement, the participants will be asked to reproduce the previous movement they just experienced, including to match the same speed as much as they can. Participants will only begin their movement after getting the movement initiation cues appearing for 1.2 s. This assessment will last for 20 repetitions. In the second block, a passive version of the matching task will be administered where the ability to sense the endpoint position of the movement will be examined. Here, after the robot presents the reference movement the participants will remain relaxed as the robot will displace again the arm in the same direction with a speed of 2 cm/s [18]. They will be required to indicate the endpoint of the reference movement by pressing the ‘Enter’ key on a keyboard. This task again consists of 20 repetitions. As with the motor test, participants will not receive any augmented feedback (haptic or reward) throughout this test.

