### Statistical analysis

All statistical analyses will be carried out using SPSS (ver. 28.0). Information obtained from the primary and secondary assessments will be recorded as text files. From the motor test data, different kinematic parameters will be computed: endpoint error and smoothness. Likewise, kinaesthetic performance will be estimated by the difference between the reference trajectory produced by the robot and the reproduced trajectory by the participants. Behavioural outcomes obtained from every training session will be computed to identify the improvements in kinematic parameters session by session: total number of successful outcomes and average endpoint error in reaching trajectories. Due to its superiority in analysing repeated-measures dataset with and without missing values, a mixed-effects model with random intercepts and slopes will be used to reveal significant differences in the outcome measures between the two groups over three time points (baseline, post day 1, and post day 30). Statistical significance will be based on *p* value threshold of 0.05. Any post hoc comparisons will be performed following the main analysis using Tukey’s tests. Cohen’s *d* will be employed to estimate the effect size of the change scores for this study. Questionnaire results will be reported via descriptive statistics (frequency analysis).

All results will be presented with 95% confidence intervals.

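### Three named primary indices, and an implied fourth, are unranked and judged at 0.05 with no control across them, so the chance of at least one false positive is about 11-19%, not 5%

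*Protocol article*

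**What the plan says.** - **Primary outcome measures:** "Two robotic-based tests will generate behavioural performance indices as the primary outcome measures". They are taken at baseline, post-day 1 and post-day 30. No index or time point is put ahead of another.
- **Statistical analysis, motor test:** "different kinematic parameters will be computed: endpoint error and smoothness".
- **Statistical analysis, kinaesthetic test:** "kinaesthetic performance will be estimated by the difference between the reference trajectory produced by the robot and the reproduced trajectory by the participants". That makes three named indices.
- **Kinaesthetic test:** the active block is followed by "a passive version of the matching task will be administered where the ability to sense the endpoint position of the movement will be examined". It has its own response, a key press at the perceived endpoint. The Statistical analysis section names no index for it.
- **Statistical analysis, model:** a mixed-effects model is to "reveal significant differences in the outcome measures between the two groups over three time points". The threshold is a p "value threshold of 0.05".
- **Statistical analysis, further comparisons:** "Any post hoc comparisons will be performed following the main analysis using" Tukey's tests.
- **Sample size:** d = 0.5, power 0.80 and alpha 0.05 give 28 participants in total. The index to which d refers is not named.

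**The concern.** The article itself sets both the primary family and the threshold. Together they let any one of three or four indices be reported as a significant primary result, each at the full 0.05. Tukey's tests do not close this gap: they deal with comparisons within one index once its main analysis is done, not with the choice among indices.

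Two uses of the results are affected. The Introduction's first aim is to establish whether adding somatosensory components gives a dependable benefit over motor training alone, and no single pre-set test answers it. The second aim is an effect size for planning a larger trial. If several unranked indices are available, the largest can be carried forward, and it would tend to be too optimistic.

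**Working it through.** **Step 1. What the sample size covers.** Inputs from the Sample size section: d = 0.5, power 0.80, alpha 0.05, total 28. The article does not name the G*Power test. The figure reproduces as a repeated-measures within-between interaction with 2 groups and 3 measurements, if one assumes f = d/2 = 0.25, a correlation of 0.5 between measurements, and sphericity:

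- noncentrality = f² × N × m / (1 − ρ) = 0.0625 × 28 × 3 / 0.5 = 10.5
- degrees of freedom = (2 − 1)(3 − 1) = 2 and (28 − 2)(3 − 1) = 52
- power = 0.812 at N = 28, and 0.778 at N = 26

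Other readings fit less well. An independent t-test at d = 0.5 needs 128 in total (two-sided) or 102 (one-sided). A paired t-test needs 34 (two-sided) or 27 (one-sided). On every reading the calculation is for one test at 0.05.

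**Step 2. Counting the primary tests.** Endpoint error, smoothness and the trajectory difference are named, which makes 3. Passive endpoint matching is implied, which makes 4. One mixed model per index covers all three time points, so the count is one main test per index: 3 to 4 tests.

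**Step 3. Chance of at least one false positive among k tests at 0.05.**

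Independent tests: 1 − 0.95^k.

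- k = 3: 1 − 0.857375 = 0.1426
- k = 4: 1 − 0.814506 = 0.1855

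For equally correlated normal test statistics (correlation ρ, two-sided, c = 1.96):

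1 − ∫ φ(u) [Φ((c − √ρ u)/√(1 − ρ)) − Φ((−c − √ρ u)/√(1 − ρ))]^k du

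| Pairwise correlation (assumed) | 3 indices | 4 indices |
|---|---|---|
| 0 | 14.3% | 18.5% |
| 0.5 | 12.5% | 15.6% |
| 0.7 | 10.9% | 13.0% |

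The article gives no correlation between indices, so the rows show a range and not an estimate.

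**Step 4. What control across indices would cost in power.** Holm's first step tests at 0.05/3 = 0.0167 or 0.05/4 = 0.0125. Under the Step 1 assumptions (N = 28, noncentrality 10.5, 2 and 52 degrees of freedom), power for one index at these levels is 0.66 and 0.62, against 0.81 at 0.05. These are floors for Holm, because its later steps use larger thresholds.

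**The case against.** The strongest case on the other side is that this is a pilot. It is meant in part to estimate an effect size, it reports Cohen's d and 95% confidence intervals, and it nowhere says that one significant index makes the trial positive. A full analysis plan, not shown here, might set a hierarchy. Measuring two domains is also deliberate, since the Discussion expects both somatosensory and motor gains. This lowers the weight of the point and argues against dictating which domain comes first. It does not remove the point: the comparative aim comes first, the sample size is powered, and the threshold and the set of primaries are stated in the article.

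Three stronger readings are tempting, and the documents do not support them.

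- **Eight tests and an error rate near 34%.** A reader might count four indices at two follow-ups: 1 − 0.95^8 = 33.7%. But both follow-ups enter one model per index, and no separate 0.05 test at each is planned. That figure also treats the same index in the same participants on the two occasions as independent.
- **Four indices as a minimum.** Three are named. The fourth is a fair inference from the passive block, but no analysis index is given for it.
- **Conflicting results from the two tests are likely.** The motor test leaves the forearm in view, as in control training, and the kinaesthetic test removes vision, as in treatment training. But the motor test also withholds augmented feedback, uses smaller targets (1.5 cm against 3.0 cm) and presents them at random, so it matches neither arm's training. Conflict is possible; nothing shows that it is likely.

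**Conclusion.** The point holds at moderate weight. The primary family has three named indices and one implied, with no ranking, a 0.05 threshold and no stated control across them. The chance of at least one false positive is about 11-19% against a nominal 5%, roughly two to four times as high. This rests on one main test per index, a count of 3 to 4, and an assumed correlation of 0 to 0.7. The two counts could move: the trajectory difference is not reduced to one metric (participants are asked to match the movement, the endpoint and the speed), and the deciding model term is not named. The stated 80% power belongs to a single test at 0.05 and to no identified index.

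**What to change.** Before outcome data are seen by arm, do one of the following.

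1. **One primary.** Name one index, defined as a single metric, with one model contrast and one time point, and make the other indices secondary. One example is the group-by-time contrast for active kinaesthetic matching error; the index and the time point are for the trial team to choose. Tie the sample size paragraph to that index. Because 28 reproduces as an overall test over three time points, recompute the power for the chosen contrast.
2. **Several primaries.** List them, say whether passive matching is one of them, and apply Holm across them. State that the 80% power refers to a single test at 0.05.

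The change is a sentence or two in the outcome, sample size and analysis sections, with no new data collection. Under option 1, the other indices can support the conclusion but not establish it. Under option 2, power for each index falls, to no less than about 62-66% under the assumptions in Steps 1 and 4.

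Under either option, report effect sizes with confidence intervals for every index, so that the planning of the larger trial does not rest on the most favourable one.

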#### Motor performance test

The motor test will evaluate the movement quality of the affected UL during planar reaching. This test will be designed and conducted in similar fashion as the training, yet no augmented feedback whatsoever will be delivered to the participants regarding their performance. The visual target of this test will also be presented one at a time at random and correspond to the targets’ positions in the training section described earlier. All visual targets in the assessment will have a diameter of 1.5 cm. The vision of their affected forearm will not be blocked. This test comprises 20 repetitions in total.

#### Kinaesthetic test

Following the motor test, participants will perform the kinaesthetic test that is essentially a joint position matching task [32], which requires them to reproduce a reference movement presented to the affected arm. The test evaluates the ability to dynamically feel the sensation of movement, as well as, to perceive the endpoint position of the reference trajectory in the absence of the vision of their affected forearm.

In the beginning of every trial, participants will be instructed to remain relaxed while the robot displaces their hand forward and backward towards a certain target position with a smooth and straight trajectory production, with a speed of 10 cm/s. Once the robot completes this reference movement, the participants will be asked to reproduce the previous movement they just experienced, including to match the same speed as much as they can. Participants will only begin their movement after getting the movement initiation cues appearing for 1.2 s. This assessment will last for 20 repetitions. In the second block, a passive version of the matching task will be administered where the ability to sense the endpoint position of the movement will be examined. Here, after the robot presents the reference movement the participants will remain relaxed as the robot will displace again the arm in the same direction with a speed of 2 cm/s [18]. They will be required to indicate the endpoint of the reference movement by pressing the ‘Enter’ key on a keyboard. This task again consists of 20 repetitions. As with the motor test, participants will not receive any augmented feedback (haptic or reward) throughout this test.

